## Abstract

**Background & Objectives::**

Poor medication adherence is an essential contributor to Pakistan’s high prevalence of uncontrolled hypertension. This study will be aimed to assess the efficacy of a one-of-a-kind developed intervention in improving medication adherence and treatment outcomes in hypertension patients.

**Methods::**

Twleve months duration long randomized controlled trial from January to December 2021 will be carried out at Shaikh Zayed Medical Complex (SZMC), Lahore. A total of 440 patients aged 18 years and older diagnosed with hypertension in the last month with non- adherence to antihypertensive therapy <80% of pills used in the last 30 days and have access to a smartphone will be randomized into either the intervention group (n=220) or the control group (n=220). For the intervention arm, a comprehensive intervention, the “Multi-Aid-Package,” consisting of seven items: written, voice, and graphics messages, animated video, educational material, and a 24/7 help service, has been designed. Standard care will be provided to the control group. The primary outcome will be improved adherence to antihypertensive medication, while the secondary outcome will be an alteration in systolic blood pressure (SBP). The analysis will be intention to treat.

**Conclusion::**

According to this study, if the multifunctional Multi-Aid-Package proves to be a useful mobile health tool for improving hypertension patients’ medication adherence, it will also significantly affect systolic blood pressure. In Pakistan and other comparable low- and middle-income countries LMICs, the Multi-Aid-Package ought to be taken into consideration as a means of enhancing adherence to medications among hypertension patients.

## INTRODUCTION

Hypertension is a growing global health problem in the 21st century. Globally, 1.13 billion people are hypertensive, and approximately 75% of people are in LMICs.^1^ About 9.4 million fatalities worldwide are attributed to hypertension, thus becoming a major cause of death.^2^ However, these fatalities are avoidable, as cardiovascular events and all-cause mortality can be decreased by reducing systolic blood pressure.^3^

Hypertension is diagnosed in 18.9% of adolescents 15 years of age or older.^4^ The prevalence rates for hypertension were reported as 58.1%.^5^ It has been noted that modifiable variables such as a sedentary lifestyle, inadequate food, and poor education may raise the chance of undetected hypertension.^6^ Poor medication adherence and factors affecting adherence should be taken into account.^7^,^8^ Poor blood pressure control results from non-adherence to medication with a reported prevalence of non-adherence was 37.7%.^9^ Non-adherence is linked to poorer blood pressure control and adverse outcomes.^10^

In LMICs, in particular, it has been discovered that using mHealth initiatives to increase drug adherence is found effective.^11^ mHealth refers to medical care delivered using cell phones, patient monitoring devices, personal digital assistants, and supplementary wireless technologies.^12^ Because of its low cost and ease of use, mHealth is an ideal tool for low-resource settings. Mobile devices, cellular communication technology, and an internet connection are needed. As stated by the Telecommunication Authority of Pakistan, 57% of the Pakistani population uses smartphones.^13^ While the evidence that mHealth can improve medication adherence is largely lacking where very few studies done in LMICs. Additionally, there is a need to better understand how these digital solutions can be seamlessly integrated into existing clinical workflows, as well as their impact on patient behavior and overall adherence. There is a gap in standardized measures for evaluating medication adherence in studies involving mHealth, making it difficult to compare results across different studies and populations.^11^,^14^ Recommendations have been made for more research in LMICs to establish a strong causal association between the effectiveness of m-health in improving medication adherence in patients with CVDs.^11^ For this purpose, More trials are required to incorporate more refined designs.^11^

Therefore, a cutting-edge model will be employed to evaluate its efficacy comparing with traditional approaches. According to our information, this research is the first of its kind a multi-model approach with all seven comprehensive components derived from the Health Belief Model (HBM) and Self-Determination Theory (SDT) related to professional guidelines, recommendations, and technology application theories, not being unitizing in such a way in preexisting literature.

### Research Objectives:

To assess the impact of a multimodal mobile health intervention on medication adherence in individuals receiving antihypertensive therapy.To assess the impact of a multimodal mobile health intervention on SBP in individuals receiving antihypertensive therapy.

### Research hypothesis:

There is no significant impact of a multimodal mobile health intervention on medication adherence in individuals receiving antihypertensive therapy.There is no significant impact of a multimodal mobile health intervention on systolic blood pressure in individuals receiving antihypertensive therapy.

## METHODS

This study is 12 months duration long overall from January to December 2021, including six months follow up period, two-arm, single-blinded, intention-to-treat randomized controlled trial. The evaluation will be performed at the pretest and posttest. This trial is designed in accordance with the SPIRIT 2013 guidelines (Fig.1).^15^

**Fig.1 F1:**
[figure not shown]
Timelines and schedule for the trial, t_x_: total follow-up time

**Fig.2 F2:**
[figure not shown]
Algorithm for trial steps

### Study Setting:

The research will be conducted at Shaikh Zayed Medical Complex (SZMC), Lahore, a public tertiary care facility. Lahore is Punjab’s provincial capital.

### Study Participants:

The study participants will be hypertensive patients registered in SZMC’s Cardiology and Medical Outpatient Departments (OPDs).

### Ethical Considerations:

The University Putra Malaysia Ethical Committee on Human Research (JKEUPM-2020-391; May 19, 2022) and SZMC, IRB (Reference number: SZMC/IRB/163/2021; dated August 3, 2021) have accepted and approved the research protocol.

### Inclusion Criteria

Aged 18 years or more.Hypertension diagnosed in at least the last month before enrolment in the study.They must be registered as hypertensive patients at a public tertiary care hospital’s cardiology and medical outpatient departments and have been prescribed antihypertensive medications.Identified as non-adherent to medication (SEAMS score and pill-counting data of less than 80%).Must be capable of reading and sending messages using a smartphone and WhatsApp.

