### Exclusion Criteria

Have travel plans in the following two months resulting in not having access to mobile signals.Patients who have had cancer in the past may need to adjust their medication.Patients with a hypertensive emergency reading of more than 220/120 mmHgPatients who report being pregnant, lactating, or three months postpartum

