### Intervention Arm:

The focus of the intervention will be to increase the adherence of those in the intervention group taking treatment for hypertension. The contents of this module will be based on the HBM and SDT.

The intervention will be a seven-item, multifaceted educational support and inimitable module for reminders called the “Multi-Aid Package” that will be delivered using a mobile phone application (WhatsApp), in addition to the standard treatment (according to the hospital’s protocol).

The module will be comprised of daily audio and textual, graphics-based reminders (GBR), and, two times a week, graphics-based messages (GBM). Reminder text, voice, and graphics for medication intake are in Urdu. Examples of such statements will be “Good Morning; it is time for your medicine.” There will be a weekly animated video presentation containing educational material on hypertension and medical and lifestyle adaptations for good Health, which resultantly improves adherence. Based on the two well-known theories, Health believe model (HBM) and Self-determination theory (SDT), an experienced team will be involved in designing a graphic-based communications series and video that improves motivation and self-efficacy for antihypertensive treatment.

The participants can also access the “Hypertension at a Glance” module to obtain complete information about their diseases, such as their etiology, diagnosis, treatment, consequences, and complications. Multi-Ad Package has been designed as a more personalized and customized approach for patients. Each component addresses to provide a highly personalized strategy for a patient-centered intervention (Table-I).

**Table-I T1:** Contents of Multi-Aid-Package.

Multi-Aid-Package Multifaceted educational and reminder module		

No.	Content Description	Frequency
1	Written message	Daily
2	Voice message	Daily
3	Graphics-based reminder (GBR)	Daily
4	Graphics-based message (GBM)	Twice weekly
5	Hypertension at a glance	Optional
5.1	PowerPoint presentation	Optional
5.2	Literature support as the convenience of participant	Optional
6	Animated video	Weekly
7	Help provided by the doctor	Optional

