### Control Arm:

Participants in the control group receive conventional care only. No intervention/ placebo will be provided to controls. There will be no way to keep them engaged except follow-ups.

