### Randomization, Sequence generation, and Allocation concealment:

A simple, complete randomization technique will be used.^19^ Initially, the formula =ROUNDUP (RAND ()*440,0 will be used in Microsoft Excel to create a random sequence. Using their unique identification numbers, participants will be randomly assigned 1:1 into each group in a parallel manner. When the sealed opaque envelopes with the screened participants’ identification numbers are opened, it will be clear which group (control or intervention) they are assigned to. Every ongoing randomization phase will be carried out by a biostatistician.

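### The listed eligibility criteria allow two members of one household, or two users of one phone number, to be enrolled and split between arms, so some controls could be exposed to the WhatsApp package

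*Protocol article*

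**What the plan says.** The relevant text is in five places in the protocol article.

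- **Inclusion Criteria.** The phone condition is ability to use the technology: "Must be capable of reading and sending messages using a smartphone and WhatsApp". The Methods part of the Abstract is looser and asks that patients "have access to a smartphone".
- **Exclusion Criteria.** One item concerns phones: "Have travel plans in the following two months resulting in not having access to mobile signals". Relatives of a participant, shared handsets and shared numbers are not mentioned.
- **Intervention Arm.** The package is "delivered using a mobile phone application (WhatsApp), in addition to the standard treatment". Table-I lists daily written, voice and graphic reminders, graphic messages twice a week and a weekly animated video, plus optional items.
- **Control Arm.** "Participants in the control group receive conventional care only".
- **Randomization, Sequence generation, and Allocation concealment.** The technique is simple randomisation of individuals by identification number: "participants will be randomly assigned 1:1 into each group in a parallel manner". Households are not linked.

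The Limitations section names self-report and social desirability bias, but not exposure of controls to the package.

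**The concern.** All participants come from the outpatient departments of one hospital, and the regular content of the package reaches the patient through a phone. The sample reminder in the Intervention Arm section is generic and could prompt anyone in the home who takes medicine. A voice message can be overheard. On a shared number, the messages arrive on the device the control also uses.

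A recruiter who follows the two lists would enrol both members of a couple, or both users of one number, if each met the remaining criteria. If the pair were split, the control would no longer be receiving conventional care alone. Any benefit that control gained would narrow the difference in adherence and in systolic blood pressure. Intention-to-treat analysis does not repair this, because the exposed control is correctly analysed as a control. At stake are some power and a somewhat understated effect.

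**Working it through.** **The plan's own figure.** The Sample Size section gives scores of 7.4 and 7.0 (difference 0.4), alpha 0.05, 30% attrition, and 220 per group or 440 in total. The readable text states neither a standard deviation nor a power, and the formula is a figure not shown. The 220 therefore cannot be reproduced from stated inputs. It is compatible with an assumed SD of 1.25, two-sided alpha and 80% power:

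- n = 2 × (1.960 + 0.842)² × 1.25² / 0.4² ≈ 153.3, rounded up to 154 per group
- 154 / 0.7 = 220

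This neither confirms the sample size nor shows it to be wrong. The power calculation below does not depend on the SD, only on the assumed starting power.

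**Step 1: from pairs to exposed controls.** Let s be the share of participants who belong to a same-household or same-number pair. There are 440 × s / 2 = 220s pairs. Under simple 1:1 allocation, a pair is split with probability 1/2, so about 110s controls have a partner in the intervention arm. As a share of 220 controls this is c = 110s / 220 = s/2.

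**Step 2: from exposed controls to the difference.** If each exposed control gains the full effect, the expected difference is 0.4 × (1 − c). Full transfer is the upper bound of the dilution; partial transfer gives less.

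**Step 3: from the difference to power.** With a normal approximation and two-sided alpha 0.05, a design with 80% power has a standardised difference of 1.960 + 0.842 = 2.802. Then

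power = Φ(2.802 × (1 − c) − 1.960).

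Example for c = 5%: 2.802 × 0.95 − 1.960 = 0.702, and Φ(0.702) = 75.9%.

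The sample size needed to restore the planned power rises by the factor 1/(1 − c)².

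| s (assumed) | pairs among 440 | c = s/2 | controls exposed of 220 | difference | power from 80% | power from 90% | sample size factor |
|---|---|---|---|---|---|---|---|
| 2% | 4.4 | 1% | 2.2 | 0.396 | 79.2% | 89.4% | 1.02 |
| 4% | 8.8 | 2% | 4.4 | 0.392 | 78.4% | 88.8% | 1.04 |
| 10% | 22 | 5% | 11 | 0.380 | 75.9% | 86.9% | 1.11 |
| 20% | 44 | 10% | 22 | 0.360 | 71.3% | 83.1% | 1.23 |

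Every value of s is an assumption. With one participant per household and per number, c from this source is zero and the stated 220 per group is unchanged.

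**The case against.** The strongest objection is that nothing in the quoted criterion is wrong. The article condenses a fuller protocol that is not shown and may hold an enrolment rule of this kind. That is possible. But the article sets out explicit inclusion and exclusion lists, with phone conditions in both, and a rule on who may enrol belongs there. Applied as written, the lists admit both members of a pair.

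The second objection concerns size, and it stands. Both people must be registered hypertensive outpatients of this hospital, non-adherent, able to use WhatsApp and enrolled, and then be split by chance. Exposing 5% or 10% of controls needs 22 or 44 pairs among 440. With 2% to 4% of participants in pairs, the loss is about 1 to 2 power points. The package is also addressed to someone else and partly given on request, so full transfer is unlikely. Any bias is towards no difference and cannot create a false benefit.

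A reader might also draw three stronger inferences that the document does not support:

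- **That the planned two-sample tests are invalid because household members are correlated.** Under individual 1:1 randomisation, positive within-pair correlation raises the variance of the arm difference for pairs in the same arm and lowers it for split pairs. With half of each expected, the two largely cancel.
- **That a shared phone breaches the Consent and Confidentiality section.** That section covers anonymised data, passwords, encryption and informing participants about data security. It makes no promise about who else uses a handset.
- **That every participant must own a phone.** This would exclude shared-phone users who create no cross-arm exposure when only one of them is enrolled.

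**Conclusion.** The point holds as a gap in the listed criteria. They allow two members of a household, or two users of one number, to be enrolled and allocated to different arms. The control of such a pair could be exposed to the package, which would weaken the contrast with conventional care and bias the difference towards zero.

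A reader might infer that the trial's effect is in fact diluted. The article does not support that: it gives no rate of shared households or phones, and no evidence that any such pair exists. Under full transfer and an assumed 80% power, the loss is about 1 to 2 points if 2% to 4% of participants are in pairs, about 4 points at 10% and about 9 points at 20%. These figures rest on pairs of two, independent 1:1 allocation, an unchanged SD and the normal approximation. The point is a cheap improvement to the plan, not a threat to its validity.

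**What to change.** 1. Add to the Exclusion Criteria that only one participant per household and per WhatsApp number is enrolled. A later household member, or a later user of the same number, is not eligible. Apply the check at screening, before the allocation envelope is opened, so that nobody is removed after randomisation.
2. At the six-month visit, ask both arms whether they saw or heard study messages or videos, and report the answers by arm. Ask this only after all outcomes have been recorded. Systolic blood pressure must be included explicitly: it is not one of the questionnaire's Sections A to D, so placing the question last in the questionnaire would not by itself protect the blinding of that measurement.

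The cost is one screening question and one follow-up question. The rule turns away one member of each pair: about 4 to 9 people per 440 candidates if 2% to 4% are in pairs (440 × s / 2), and more if pairs are more common. The sample size does not change.

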### Exclusion Criteria

Have travel plans in the following two months resulting in not having access to mobile signals.Patients who have had cancer in the past may need to adjust their medication.Patients with a hypertensive emergency reading of more than 220/120 mmHgPatients who report being pregnant, lactating, or three months postpartum

### Intervention Arm:

The focus of the intervention will be to increase the adherence of those in the intervention group taking treatment for hypertension. The contents of this module will be based on the HBM and SDT.

The intervention will be a seven-item, multifaceted educational support and inimitable module for reminders called the “Multi-Aid Package” that will be delivered using a mobile phone application (WhatsApp), in addition to the standard treatment (according to the hospital’s protocol).

The module will be comprised of daily audio and textual, graphics-based reminders (GBR), and, two times a week, graphics-based messages (GBM). Reminder text, voice, and graphics for medication intake are in Urdu. Examples of such statements will be “Good Morning; it is time for your medicine.” There will be a weekly animated video presentation containing educational material on hypertension and medical and lifestyle adaptations for good Health, which resultantly improves adherence. Based on the two well-known theories, Health believe model (HBM) and Self-determination theory (SDT), an experienced team will be involved in designing a graphic-based communications series and video that improves motivation and self-efficacy for antihypertensive treatment.

The participants can also access the “Hypertension at a Glance” module to obtain complete information about their diseases, such as their etiology, diagnosis, treatment, consequences, and complications. Multi-Ad Package has been designed as a more personalized and customized approach for patients. Each component addresses to provide a highly personalized strategy for a patient-centered intervention (Table-I).

**Table-I T1:** Contents of Multi-Aid-Package.

Multi-Aid-Package Multifaceted educational and reminder module		

No.	Content Description	Frequency
1	Written message	Daily
2	Voice message	Daily
3	Graphics-based reminder (GBR)	Daily
4	Graphics-based message (GBM)	Twice weekly
5	Hypertension at a glance	Optional
5.1	PowerPoint presentation	Optional
5.2	Literature support as the convenience of participant	Optional
6	Animated video	Weekly
7	Help provided by the doctor	Optional

### Control Arm:

Participants in the control group receive conventional care only. No intervention/ placebo will be provided to controls. There will be no way to keep them engaged except follow-ups.

### Outcome Measures

### Primary Outcome:

The change in adherence to antihypertensive medication will be the primary outcome. The primary endpoint will be assessed using the SEAMS and pill counts used over a certain period.^14^,^16^ The adherence to antihypertensive medication will be assessed at baseline and six months.

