### Data Collection:

A four section validated and pretested questionnaire in Urdu and English will be utilized. Section-A will involve the collection of data on pertaining to health and sociodemographics. Section B will be the the SEAMS-related scale.^20^ A 13 item measure called SEAMS is used to evaluate medication adherence.^20^ The scale’s scores go between 13 and 39. Greater levels of scores are correlated with better scores.

In Section-C, participants will be questioned about the number of pills used. The number of tablets taken over a certain time period divided by the total number of tablets prescribed for that time period was used to calculate the non-adherence rates.^16^ If the adherence percentage is 80% or higher, it will be considered adherent; if it is less than 80%, it will be regarded non-adherent. The literature also reports on this threshold. 14,16

Finally, Section-D will be a survey of the post-intervention follow-up to determine the intervention’s acceptability. At the final follow-up interview, participants in the intervention arm will be evaluated for end-user suggestions.

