### Statistical Analyses:

Intention-to-treat analysis will be applied. The mean and standard deviation/ median and interquartile ranges will be presented. Frequencies and percentages will be used to depict categorical data. Differences in adherence scores and SBP between two groups (Independent samples t-test/ Mann–Whitney U test) at six months will be applied. For differences in adherence scores and SBP in one group between two time points, a Paired samples t-test /Wilcoxon signed-rank test will be conducted on the data. P < 0.05 will be used as the significance test. Data will be reported as to why it is missing (Table-II). All analysis will be made using SPSS and R-Studio.

**Table-II T2:** Methods for data analysis

Independent variables (IDVs)	Dependent variables (DVs)	Type of analysis
Categorical (groups)	Continous (SEAMSscore)	(Independent samples t-test/ Paired samples t-test) (Wilcoxon signed-rank test/ Mann–Whitney U test)
Categorical (groups)	Continous (systolic blood pressure)	(Independent samples t-test/ Paired samples t-test) (Wilcoxon signed-rank test/ Mann–Whitney U test)
Categorical (all IDVs)	Categorical (all IDVs)	Chi-squared test

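### One primary endpoint rests on two different adherence measures with no rule for which decides, and Table-II does not clearly give pill count a between-arm test

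*Protocol article*

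**What the plan says.** The Primary Outcome section of the protocol article states "The change in adherence to antihypertensive medication will be the primary outcome" and continues "The primary endpoint will be assessed using the SEAMS and pill counts used over a certain period", with assessment at baseline and six months.

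The Data Collection section describes the two instruments. SEAMS has 13 items, and "The scale’s scores go between 13 and 39". Pill count is tablets taken divided by tablets prescribed over a period, then classed: "If the adherence percentage is 80% or higher, it will be considered adherent; if it is less than 80%, it will be regarded non-adherent".

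The Statistical Analyses section plans the comparison between arms as follows: "Differences in adherence scores and SBP between two groups (Independent samples t-test/ Mann–Whitney U test) at six months will be applied". It adds "P < 0.05 will be used as the significance test". In Table-II the only adherence variable listed as dependent is the one that begins "Continous (SEAMSscore"; the other named outcome is systolic blood pressure. The last row, a chi-squared test, carries the same label, all IDVs (independent variables), in both the independent and the dependent column.

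The Sample Size section plans on a single adherence score of 7.4 against 7.0, with alpha 0.05 and 220 per arm after 30% attrition. It does not name the instrument.

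**The concern.** A score and a dichotomised percentage can disagree. A package of reminders and education could move a questionnaire score without moving tablets taken, or the reverse. With no deciding rule, discordant results leave the primary question without a pre-specified answer, and the favourable measure could be reported as the primary one.

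The missing rule also fixes the trial's operating characteristics. An either-suffices rule at 0.05 per test does not hold the 5% error rate. A both-required rule holds it but loses power. The article sets 0.05 per test without saying which rule applies.

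Finally, the analysis table does not match the endpoint: part of the primary endpoint has no clearly assigned treatment comparison.

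**Working it through.** **1. Can the other sections identify the primary measure?**

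- Inclusion Criteria: non-adherence is judged by SEAMS and pill count together.
- Abstract: the entry condition is given by pills alone.
- Table-II: SEAMS is the only adherence outcome named.
- Sample Size: 7.4 and 7.0 are called adherence scores. Read as scores, both lie below the SEAMS minimum of 13, and they are not presented as tablet percentages.

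These point in different directions, so the choice cannot be recovered from the text.

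**2. The plan's own figure.** The text gives neither the standard deviation (SD) nor the power, and the formula is in a figure not shown, so 220 per arm can be neither confirmed nor refuted. It is attainable. After 30% attrition, 220 × 0.70 = 154 are evaluable. With an assumed SD of 1.25, 80% power and two-sided 0.05:

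n = 2 × (1.25/0.4)² × (1.960 + 0.842)² = 2 × 9.766 × 7.85 ≈ 153.3, rounded up to 154; 154/0.70 = 220.

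**3. Error and power under the two possible rules.** Inputs: two two-sided tests at 0.05 (critical value 1.960). The correlation between the test statistics is not in the documents and is varied. The power on each measure is assumed to be 80%.

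- Either suffices: error = 1 − P(|Z₁| ≤ 1.960 and |Z₂| ≤ 1.960). At correlation 0 this is 1 − 0.95² = 0.0975.
- Both required: joint power = P(Z₁ ≤ 0.842 and Z₂ ≤ 0.842). At correlation 0 this is 0.80² = 0.64.

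| Assumed correlation | Type I error, either suffices | Joint power, both required |
|---|---|---|
| 0 | 0.0975 | 0.640 |
| 0.3 | 0.0951 | 0.666 |
| 0.5 | 0.0907 | 0.687 |
| 0.7 | 0.0835 | 0.713 |
| 0.9 | 0.0704 | 0.750 |

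Under the both-required rule the type I error is at most 0.05. With one named primary, 0.05 needs no adjustment.

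**4. Cost of keeping two primaries.** Holm's first step tests at 0.025 (critical value 2.241). With 154 evaluable per arm, and a design that has 80% power at 0.05, power is Φ(1.960 + 0.842 − 2.241) = Φ(0.56) ≈ 0.71.

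**5. Table-II against the endpoint.** The endpoint needs a comparison of SEAMS and one of pill count. Table-II supplies the first. Its chi-squared row names no outcome at all.

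**The case against.** Four points can be made on the other side.

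- **A slip in the table.** The second label in the chi-squared row stands in the dependent-variable column and may be a slip for all DVs (dependent variables). The one binary outcome class that the article defines is adherent or not at 80%, so the row may be meant for it. The plural adherence scores in the text could also take in the pill percentage. This stands as far as it goes: a reader might infer that pill count never receives a treatment comparison, and the documents do not support so flat a statement. But neither reading is written, and they lead to different analyses, a chi-squared test on a class or a t-test on a percentage.
- **The error rate depends on an unstated rule.** This also stands. A reader might infer that the trial runs at nearly 10% type I error. That needs both an either-suffices rule and independent measures. The article joins the two with the word and, which may mean both are required. Independence is unlikely, because the same patients report the same behaviour.
- **The 30 days in the Abstract.** A reader might infer a conflict with the unspecified period in the Primary Outcome section. There is none: the 30 days describe eligibility, not the six-month outcome.
- **Details belong in the analysis plan.** Alpha sharing and test order often do, and their absence is not the point here. The article itself states the primary endpoint and prints an analysis table that does not match it.

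**Conclusion.** The concern holds in limited form. One primary endpoint is assessed by two different variables without a deciding rule, and the analysis table does not clearly assign one of them a comparison between arms.

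Its size depends on the rule left unstated: type I error of about 7.0% to 9.8% if either measure suffices, or joint power of about 64% to 75% if both must succeed. These ranges assume correlations from 0.9 to 0 for the error and from 0 to 0.9 for the power, and 80% power on each measure; none of these values is in the documents. The ambiguity itself needs no assumption. It can be read directly from the Primary Outcome, Data Collection and Statistical Analyses sections, and it should be resolved before results by arm are known.

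**What to change.** Before outcome data are seen:

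1. Name one measure, in one form, as the sole primary at two-sided 0.05. The SEAMS score at six months is the natural choice, because Table-II already analyses it; what matters most is that one is chosen.
2. Make pill count a secondary outcome in one stated form, for example adherent at 80% or more, with the same look-back window at baseline and six months.
3. Correct the chi-squared row of Table-II to pill-count adherence (80% or more) by arm, and report the risk difference with its 95% confidence interval.
4. Reconcile the Sample Size section with the measure named. If SEAMS is chosen, say what 7.4 and 7.0 measure, since as scores they are not on the 13 to 39 scale. Until then, nothing shown supports 220 per arm for that endpoint.

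The cost is revised wording, one added table row and a restated sample-size justification. The downside is that a significant result on the other measure alone can no longer be claimed as primary success.

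If the sponsor keeps two primaries with Holm, power on each is lower: about 71% at the 0.025 level with 154 evaluable per arm, if power at 0.05 is assumed to be 80%. The plan should then state that loss.
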